Type of OACs: date of start and end of treatment and dosages of the OACs under study (DOACs and VKA) will be collected.Sociodemographic data: age (time between date of birth and the event), Health Management Area, reference hospital, province.Contacts with the PHS-A (episode count and attendance indicators recorded in the last year and the annual average recorded during the study period) in primary care centres, hospitals, at home, and in the emergency department.Comorbidities: diagnosed health problems and their associated dates will be included (S3 Table). Comorbidity will be defined as the presence of an active diagnosis in the available databases (emergency, hospital and primary care) in the 12 months prior to the date of the event.Variables related to medication use: dates of start and end of treatment, dosage. The use of medication related to increased risk of bleeding or prevention of bleeding will be analysed according to the Anatomical Therapeutic Chemical (ATC) classification of the WHO Collaborating Centre for Drug Statistics Methodology (www.whocc.no/) (S4 Table).CHADS_2_ and CHA_2_DS_2_-VAS_C_ (Thromboembolic Risk Assessment) and HAS-BLED (Bleeding Risk Assessment) scales: the scores on these scales will be calculated at the date of the patient’s inclusion in the study, using the information available in the previous 12 months.All variables or diseases included in the CHADS2 and CHA2DS2-VASC scores will be considered for calculation of the total thromboembolic risk score. Diagnoses of “previous stroke”, “ischaemic stroke” (excluding haemorrhagic stroke), “TIA”, "systemic embolism", "pulmonary embolism" (hospital care diagnoses) and “thromboembolic events” (primary care diagnoses) will be grouped into a single section of the CHA2DS2-VASC scores. A history of “myocardial infarction", "angina pectoris" and "peripheral arterial disease" (diagnoses recorded in both hospital and primary care) will be considered as "vascular disease". The total score of the scale will be between 0 and 9 points.Intracranial haemorrhages and haemorrhagic strokes will be counted as "previous cerebrovascular accident" on the HAS-BLED Scale. Records with an ICD-9 or ICD-10 identification for renal or liver failure, or their primary care equivalents, will be collected. Safety outcome events of the study (intracranial or gastrointestinal haemorrhage) previously experienced by the patient will be considered as “Previous history of or predisposition to bleeding". "Labile INR" will not be included in calculations on this scale, since it applies to just one of the groups of medicines under study (VKA). Drugs predisposing to bleeding will be included in the calculation of bleeding risk (S4 Table). The “alcohol consumption” variable will not be included in the scale, as this information is not available in the vast majority of cases. The total score of the scale will be between 0 and 7 pointsPredictor variables will be analysed for associations with events based on information available in the previous 12 months.

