
### Data analysis plan

Cohorts will be compared by matching patients based on their propensity scores (PS) to be treated with acenocoumarol versus each of the four DOACs and versus warfarin in order to counteract the risk of selection bias when comparing the 5 different cohorts of OACs against the reference treatment cohort (acenocoumarol). This can be viewed as an attempt to emulate a randomized experiment (quasi-experimental study).

We consider that *propensity score matching* is of relevance in new RWD studies, and is more appropriate than other methods, such as *inverse probability of treatment weighting* (IPTW). After consulting the literature, matching cases by propensity score at the beginning of the study seems to be a more suitable epidemiological approach than first calculating a propensity score and assigning a weight to each case, before calculating the IPTW, unlike other publications on RWD in oral anticoagulation [10, 14, 15]. This strategy will help to control for selection bias by creating case-matched treatment groups that will be more comparable based on baseline patient characteristics.

A longitudinal registry will be created in a database that will later be imported with the Excel, R and Stata statistical packages together with the definitions of the variables described. The risk of events (effectiveness and safety) in patients treated with VKA and DOACs will be assessed.

Quantitative variables will be summarised as means and standard deviations, and in case of highly skewed distributions, as median and interquartile ranges (p25, p75). Frequency tables and percentages will be used for non-quantitative variables. Point estimates and 95% confidence intervals will be obtained for the different statistical analyses.

Contingency tables will be developed and the chi-square test, chi-square with continuity correction, and Fisher’s exact test (for 2x2 tables with small samples) will be applied to assess the relationship between two qualitative variables. In our analysis, parametric statistical tests will be used when variables fulfil the assumptions of normality and independence. Parametric tests are usually more powerful and sensitive when the data follow a normal distribution, allowing us to obtain more accurate and meaningful results. Non-parametric tests will be applied if the assumption of normality is not met.

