Univariate survival analysis (for time-censored data) will be performed using Kaplan-Meier curves to represent the frequency of occurrence of different events or diseases over time and, where appropriate, in relation to different categories of a variable (age groups, sex, province, etc.) [18].

Survival probabilities, median and quartiles will be calculated, generating statistics and plotting survival functions for each study group.

The log-rank test will be used to test the equality of survival time distributions between different groups.

A preliminary univariate analysis will be performed to identify variables related to time-to-event occurrence (comparing event incidence density to person time to follow-up for different categories of variables).

To analyze this database, confounding variables identified in previous studies will be taken into account. Statistical analyses will include bivariate analysis (association between type of anticoagulant used and each of the other study variables); the Mantel-Haenszel test (analysis stratified by a third variable), as well as multivariate analysis.

A multivariate survival analysis will be performed using Cox proportional hazards or time-dependent Cox regression to control for the effect of confounding variables in the study. Cox regression will be used to create time-to-event models, considering both categorical and continuous predictor variables (covariates) as hypothetical predictors. Potential confounding variables include: age, sex, contacts with health service, comorbidities, concomitant medications, CHA2DS2-VASC and HAS-BLED scores, and previous ischemic and bleeding events.

Determination of the risk of outcomes among DOACs or warfarin versus acenocoumarol (reference) users will be obtained by calculating the specific instantaneous risk ratios for each comparison (Hazard Ratio) (HR) using multivariate Cox regression models. Adjusted survival curves will be used to represent how event risks will evolve over time after adjusting for different confounding variables.

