A significance level of 0.15 will be used in preliminary univariate analysis to enable the selection of variables for inclusion in multivariate analysis. Once these variables have been selected, a multivariate analysis will be performed to select the final model. The analysis will be performed for both effectiveness and safety events. HRs and 95% confidence intervals (95% CIs) will be calculated for the selected variables once the application requirements have been validated.

The characteristics of the total study population and of each of the cohorts based on the first OAC used will be reported in the corresponding tables as percentages, means (standard deviation) or medians (interquartile range). Incidence rates will be calculated as the number of events divided by the corresponding denominator of person-time in follow-up.

Intention-to-treat analysis will be carried out by categorising each patient according to the first anticoagulant treatment they start taking in the study period, provided that they have not taken any other anticoagulant for at least 12 months previously (“washout period”) and regardless of any possible changes in type of anticoagulant or non-adherence that may occur in the follow-up period (Fig 3).

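### A contact count averaged over the study period, and so partly measured after treatment start, may be adjusted for as a confounder in the Cox models

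*Protocol article*

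**What the plan says.** In the protocol article, Outcome measures lists contacts among the independent variables, to be analysed as relevance and availability allow. It gives two measures: "episode count and attendance indicators recorded in the last year and the annual average recorded during the study period". They are counted "in primary care centres, hospitals, at home, and in the emergency department". No index date is attached to either. The risk scores, by contrast, are tied to the date of inclusion. The same list ends by saying that predictors rest on the previous 12 months, without naming the date from which those months run back.

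The Data analysis plan states: "Potential confounding variables include: age, sex, contacts with health service, comorbidities, concomitant medications", followed by the risk scores and previous events. The adjustment is made "using Cox proportional hazards or time-dependent Cox regression to control for the effect of confounding variables in the study", and these models yield the hazard ratios against acenocoumarol. Entry is screened: "A significance level of 0.15 will be used in preliminary univariate analysis to enable the selection of variables for inclusion in multivariate analysis". Patients are analysed by the first OAC they start, whatever happens later. On matching, the plan says that "matching cases by propensity score at the beginning of the study seems to be a more suitable epidemiological approach", and it describes the matching characteristics as baseline ones.

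**The concern.** An analysis by first treatment, presented as emulating a randomised experiment, should adjust only for what was known when treatment began. An average over January 2012 to December 2020 also contains follow-up time, and it can contain time after the event. Two things can then feed into it.

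- **The drug.** If one drug group needs more visits than the other, the average is partly a result of treatment.
- **The outcome.** The safety endpoint consists of haemorrhages leading to admission, and hospital and emergency contacts are counted.

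Conditioning on such a variable can move the hazard ratio away from the true value even when the treatment groups were comparable at the start. The four DOAC versus acenocoumarol comparisons are the ones exposed.

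**Working it through.** The article gives no contact rates, event rates or expected hazard ratios, so there is no figure of the plan to reproduce. The check reads the text first and then illustrates the effect.

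**1. What the average covers.** The study period is nine calendar years. For a patient who starts in January 2012 nearly all of it lies after treatment start; for one who starts in December 2020 almost none does. The covariate therefore means different things for different patients.

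**2. Simulation inputs (all assumed).** 20,000 patients randomised 1:1 to DOAC (A = 1) or acenocoumarol (A = 0); uniform entry over 9 years; frailty U ~ N(0,1); half of events fatal; two replicates.
- Event hazard: 0.06 × exp(0.5U) per year in both arms, so the true hazard ratio is 1.0.
- Contacts before index: Poisson with mean 6 × exp(0.4U) in the year.
- Contacts per year after index: 6 × exp(0.4U) + m × (1 − A), where m is the extra VKA visits.
- Model: Cox on A and log(1 + contacts).

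**3. Why the hazard ratio can rise.** Take m = 6 and two patients who both have 12 contacts a year. For the acenocoumarol patient, 12 − 6 = 6 are not monitoring, so U = 0. For the DOAC patient, 6 × exp(0.4U) = 12 gives U = ln 2 / 0.4 = 1.73. Their hazards differ by exp(0.5 × 1.73) = 2.38, although the drugs are equivalent.

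**4. Why it can fall.** Divide the total by a fixed nine years instead, and a low total marks early death. A total of 54 contacts in follow-up at U = 0 means 54 / 12 = 4.5 years on acenocoumarol, but 54 / 6 = 9 years on a DOAC. At equal totals the acenocoumarol patient was observed for less time.

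**5. Results (adjusted hazard ratio, DOAC versus acenocoumarol, truth 1.0).**

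| Contacts adjusted for | m = 0 | m = 6 | m = 12 |
|---|---|---|---|
| 12 months before index | 0.98 | 0.98 | 0.98 |
| Average per year of follow-up | 0.98 | 1.43 | 1.68 |
| Average per year alive in the study period | 0.98 | 1.55 | 1.77 |
| Total divided by nine years | 0.98 | 0.69 | 0.46 |

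The follow-up average uses a denominator of at least half a year. The last row depends on deaths: with no fatal events, m = 12 gave 2.45 instead of 0.46. Three extra contacts a year on the DOAC only, with the underlying contact rate known exactly, gave 0.57.

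**6. A second set of assumptions.** With 8 baseline contacts a year, 4 extra VKA contacts and an event rate of 0.06, a true hazard ratio of 1.0 became 1.40 (per year alive) or 0.71 (fixed denominator). A true 0.7 became 1.00 or 0.50.

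**7. Outcome contacts alone.** With no difference in contacts between arms but 8 extra contacts per event, the adjusted value was 0.98. Under these assumptions, bias in the drug effect needed a difference in contacts between arms.

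**The case against.** The text does not commit to adjusting for the average. Two measures are defined, contacts are only potential confounders, entry depends on the 0.15 screen, and the closing sentence of the list limits predictors to the previous 12 months. This stands in part: the defect is an unresolved choice, not a confirmed plan to use the average. But that sentence contradicts the average and has no index date, and comorbidity in the same list is dated back from the event. Nor is the screen a safeguard, because a variable that counts event admissions is likely to pass it.

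The option of time-dependent Cox regression does not settle it either. The handling of contacts there is not described, and an average over the whole period is not a value known at each point in time.

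A reader might infer three stronger things that the documents do not support.

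- **That matching uses the average.** The Data analysis plan places matching at the start on baseline characteristics and does not name contacts.
- **That the plan itself says VKA monitoring adds contacts.** The nearest text explains why labile INR is left out of HAS-BLED: "since it applies to just one of the groups of medicines under study (VKA". It says nothing about visit counts. The limitations also mention prior authorisation for DOACs, which could add contacts on that side.
- **That DOACs will look harmful.** The results above fall on both sides of 1.

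**Conclusion.** The point holds as a correctable fault in the stated text. A contact measure that includes time after treatment start is defined, its variable class is assigned to Cox adjustment, and nothing restricts the adjustment to contacts before the index date. This can bias the four DOAC comparisons. Warfarin versus acenocoumarol is largely spared, since both are VKAs.

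Sign and size are undetermined. They depend on whether monitoring visits are counted, which arm generates contacts, the denominator of the average, how strongly frailty drives events and how many events are fatal; the article gives none of these. The simulated values rest wholly on assumed inputs and are not estimates for this study. They show that the definition alone could decide the direction, and that contacts before the index date carried no material bias in the true-null scenarios (0.98 to 0.99).

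**What to change.** - In the Cox models, and in the propensity score if contacts are included there, use only contacts in the 12 months before the first OAC dispensing.
- Keep the study-period average, if wanted, as a descriptive result on resource use.
- In Outcome measures, tie the last-year count and the closing 12-month sentence to the index date.
- In the Data analysis plan, state which contact measure is meant in the confounder list and whether it enters the matching, so that the two sections agree.

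The cost is wording. The counts come from the same database, and the plan already needs a 12-month look-back for its washout and risk scores. The change should be made before analysis.

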### Outcome measures

The pre-specified effectiveness outcomes will be the incidence of new diagnosis among the following list: transient ischaemic attack, systemic embolism, pulmonary embolism, ischaemic stroke and all-cause mortality, as a combined effectiveness endpoint.

Safety outcomes will be the incidence of new diagnosis of major haemorrhages leading to hospital admission (gastrointestinal and intracranial haemorrhages). They will be considered as a combined safety endpoint. Post-traumatic bleeding will be excluded.

All effectiveness and safety events will be associated with their dates of onset and identified using the corresponding International Classification of Diseases (ICD-9 or ICD-10 codes) (S2 Table).

Time-to-event will be defined as the number of days elapsed from the date of initiation of treatment (dispensing at pharmacy) until the date of the event, death or the end of study period (December/2020).

The following independent variables will be analysed according to relevance and availability in PHS-A databases:

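### Age and comorbidities, both Cox adjustment covariates, are defined at the date of the outcome event instead of at first dispensing

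*Protocol article*

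**What the plan says.** All references are to the protocol article, Methods and analysis.

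- **Outcome measures, time-to-event.** Time runs "from the date of initiation of treatment (dispensing at pharmacy) until the date of the event, death or the end of study period (December/2020". Time zero is the first dispensing, and the event is the effectiveness or safety outcome.
- **Outcome measures, independent variables.** The sociodemographic item lists "age (time between date of birth and the event". The comorbidity item asks for an active diagnosis in the databases "emergency, hospital and primary care) in the 12 months prior to the date of the event".
- **Outcome measures, risk scores.** CHADS2, CHA2DS2-VASc and HAS-BLED are calculated at the date of inclusion, "using the information available in the previous 12 months".
- **Outcome measures, contacts.** Health-service contacts are recorded for the last year and also as a yearly mean over the whole study period.
- **Data analysis plan, Cox models.** "Potential confounding variables include: age, sex, contacts with health service, comorbidities, concomitant medications", followed by two of the risk scores and previous events. The model is "Cox proportional hazards or time-dependent Cox regression to control for the effect of confounding variables".
- **Data analysis plan, matching.** The authors prefer "matching cases by propensity score at the beginning of the study", to obtain "groups that will be more comparable based on baseline patient characteristics".

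**The concern.** A covariate used to remove confounding at treatment start has to be known at treatment start. Age and comorbidity are instead tied to the date on which the outcome occurs. Three problems follow.

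1. A patient who never has an event has no event date, and no substitute date is given.
2. Age at the event is age at start plus time to event, so part of the outcome is built into the covariate.
3. The comorbidity window moves into the treatment period. It can then record consequences of the drug, or conditions that lie between the drug and the outcome.

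The adjusted hazard ratios of the four DOACs and warfarin against acenocoumarol are the main result. If the adjustment set is extracted as defined, baseline confounding is only partly removed and part of a real drug effect may be adjusted away.

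**Working it through.** **1. What the event is.** The article uses separate terms for the start of treatment and for inclusion in the study. In the time-to-event definition, the event ends follow-up. Read literally, the age and comorbidity definitions therefore point to the outcome date.

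**2. Age.** Let A be age at first dispensing and t the time from dispensing to the event or end of follow-up. Age as defined is A + t. Take two patients who both start at 75. One has an event after 1 year, so the covariate is 75 + 1 = 76. The other is event-free for the full nine calendar years 2012–2020. If the end of follow-up is used for lack of any rule, the covariate is 75 + 9 = 84. Their baseline ages are identical, yet the event-free patient counts as 8 years older. The estimated effect of age shrinks, and so does the adjustment for it.

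**3. Comorbidity window.** Relative to dispensing, the window runs from t − 1 to t years. Its pre-treatment part is max(0, 1 − t):

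- event at 0.5 years: 0.5 years before and 0.5 years after dispensing;
- event at 1 year or later: nothing before dispensing.

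For any event after the first year, the whole window lies on treatment. A diagnosis from before dispensing counts only if it is still active then.

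**4. Time-dependent Cox regression.** That model needs, at each event time, the current covariate value of every patient still at risk. One value per patient, taken at that patient's own event date, does not supply this. Conditions acquired after baseline may also lie on the causal path from the drug.

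**5. Size, illustration only.** The article gives no event rates or sample size, so there is no figure to reproduce and every input here is an assumption: mean age 75 (SD 9) in one arm and 3 years more in the other; hazard 8 per 100 person-years at age 75; age hazard ratio 1.06 per year; treatment hazard ratio 1.0; follow-up uniform on 0–9 years in one arm and on 0–4 or 0–9 years in the other; 12,000 patients before matching; 20 replicates. Patients without an event take their age at the end of follow-up. Matching is 1:1 on baseline age.

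| Analysis | Follow-up | HR, age at start | HR, age at event or end |
|---|---|---|---|
| Unmatched | 9 vs 4 years | 1.00 | 1.15 |
| Unmatched | 9 vs 9 years | 1.00 | 1.11 |
| Matched | 9 vs 4 years | 1.00 | 1.05 |
| Matched | 9 vs 9 years | 1.00 | 1.00 |

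Figures for age at event or end varied between repeated simulations: 1.13–1.16, 1.10–1.11, 1.04–1.06 and 0.99–1.00, in the order of the table. Without matching, the estimated age hazard ratio falls from 1.06 to about 1.02–1.03.

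A second unmatched simulation moved both age and comorbidity to the end date. It assumed a baseline comorbidity in 30% with hazard ratio 1.8, and new comorbidity at 0.06 per year doubling the hazard. A true treatment hazard ratio of 1.0 became about 1.08–1.14, and a true 0.8 became about 0.87–0.92. Start-date covariates gave 0.99–1.00 and 0.80–0.81. With a drug that halves new comorbidity and has no direct effect, the estimate moved from 0.94 to 1.05.

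**The case against.** The strongest reply is that the main control of confounding is propensity score matching, which the Data analysis plan places at the start of the study and on baseline characteristics. A reader might infer that the event-date variables feed the propensity score, so that matching no longer balances the cohorts. The article does not say so. The score's covariate list is not given, and an article may leave it to the full protocol. What remains is that the article offers no other definition of age or comorbidity, so the matching set has to be clarified.

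Other points also carry weight:

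- Matching on baseline age removes most of the simulated shift. What is left depends on unequal follow-up, and the Limitations section plans to define the follow-up period from when the drugs were marketed. The 1.15 is therefore not an estimate of the bias in the planned matched comparison.
- The inclusion-date risk scores keep some baseline risk in the Cox models. Age and comorbidities are nevertheless listed separately from the scores and enter in their own right.
- The closing sentence on predictors from the previous 12 months names no reference date. It should not be read as further evidence of event anchoring.
- A reader might expect diagnoses made during the work-up of a stroke or bleed to be counted as prior comorbidity. The window ends before the event date, and the article gives no basis for a frequency. Only on-treatment diagnoses made before the event are clearly within the definition.

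The wording may be a slip for the index date. A stated definition still drives the data extraction, so the slip needs correcting. Because a rule is stated, this is more than detail left to an analysis plan.

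**Conclusion.** The point holds for the Cox adjustment. As defined, age and comorbidity are taken at the outcome date, have no stated value for patients without an event, contain follow-up time and can reflect time on treatment. This contradicts the inclusion-date anchor of the risk scores and the stated intention to match on baseline characteristics. The option of time-dependent Cox regression does not repair it.

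For the propensity score, the documents support only an ambiguity to resolve. They do not support the conclusion that matching fails.

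The size cannot be derived from the article. On the assumed inputs with no true effect, the shift from end-date age is about 11–15% in the hazard ratio without matching, about 5% after matching with unequal follow-up, and about nil after matching with equal follow-up. The matched figures cover age alone under a null effect. They do not show what happens to a real effect or to comorbidities acquired on treatment. The case for correction rests on the definitions, not on these figures.

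**What to change.** In Outcome measures, replace the event by the date of first oral anticoagulant dispensing as the reference date for age and for comorbidities, with the 12-month look-back already used for the risk scores. Apply the same index date to concomitant medication, prior ischaemic and bleeding events, and health-service contacts. Drop the mean number of contacts over the study period as an adjustment covariate. Give the sentence on predictors an explicit reference date. State in the Data analysis plan that these index-date values are used in both the propensity score and the Cox models, and keep diagnoses made after dispensing for description only.

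The cost is a rewording and a changed anchor date in the data extraction. The dispensing date is already time zero and diagnosis dates are already collected, so no new data are needed.

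### HAS-BLED cerebrovascular item is filled only with haemorrhagic events that also score as previous bleeding; ischaemic stroke, on the natural reading, scores nothing

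*Protocol article*

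**What the plan says.** The scoring rules are in the protocol article, Methods and analysis, Outcome measures, in the list of independent variables.

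- Stroke item of HAS-BLED: "Intracranial haemorrhages and haemorrhagic strokes will be counted as 'previous cerebrovascular accident' on the HAS-BLED Scale".
- Bleeding item of HAS-BLED (the quote stops just before the last word of the item's name): "Safety outcome events of the study (intracranial or gastrointestinal haemorrhage) previously experienced by the patient will be considered as “Previous history of or predisposition to".
- Ischaemic stroke is placed in the thromboembolic section of CHA2DS2-VASc, in a list that includes "ischaemic stroke” (excluding haemorrhagic stroke), “TIA”, 'systemic embolism', 'pulmonary embolism' (hospital care diagnoses"). No sentence places it in HAS-BLED, and none excludes it.
- Two HAS-BLED components are dropped, each with a reason. For the INR component: "Labile INR' will not be included in calculations on this scale, since it applies to just one of the groups of medicines under study (VKA"). For alcohol: "The “alcohol consumption” variable will not be included in the scale, as this information is not available in the vast majority of cases".
- The modified score is stated to run from 0 to 7.
- On timing, with a look-back of 12 months: "the scores on these scales will be calculated at the date of the patient’s inclusion in the study, using the information available in the previous".

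The Data analysis plan lists these among the potential confounders: "CHA2DS2-VASC and HAS-BLED scores, and previous ischemic and bleeding events". Covariates enter the multivariate models after univariate screening at a significance level of 0.15.

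**The concern.** An item labelled for any previous cerebrovascular accident is filled with bleeding events alone, and most of those events also score the next item. A patient with a past intracranial bleed gets two points for one event. A patient with a past ischaemic stroke, which the label plainly covers, appears to get none. The article justifies its removal of labile INR and alcohol but gives no reason for this rule, so it does not read as a deliberate change.

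HAS-BLED is the study's measure of bleeding risk at inclusion and a candidate confounder, and intracranial haemorrhage is one of the two components of the combined safety endpoint. If the type of past event affects which anticoagulant is chosen, the mis-scoring could differ between cohorts. The article makes this plausible. Its Limitations section expects selection in the choice of anticoagulant, and its Introduction reports a cited study with less intracranial haemorrhage on dabigatran and rivaroxaban than on acenocoumarol, the reference here. It does not show that such channelling occurs.

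**Working it through.** **1. The stated range.** The article does not reproduce the full scale. Assume nine one-point items, of which two are dropped: 9 − 2 = 7, which agrees with the stated maximum. Five of the remaining seven items are unrelated to stroke or bleeding history. The stroke and bleeding items together give at most 2 points under every rule below, so the maximum is 5 + 2 = 7 each time. The range is consistent and does not depend on how the stroke item is filled.

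**2. Points from the stroke and bleeding items.** Let I, H and G be 0/1 indicators of previous ischaemic stroke, intracranial haemorrhage and gastrointestinal haemorrhage. H is taken to meet the study's safety definition.

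- Rule A, as written with the stroke sentence read as complete: score = H + max(H, G).
- Rule B, ischaemic stroke also scores the stroke item: score = max(I, H) + max(H, G).
- Rule C, as B but with intracranial haemorrhage kept out of the bleeding item: score = max(I, H) + G.

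| Previous events | A | B | C |
|---|---|---|---|
| None | 0 | 0 | 0 |
| G | 1 | 1 | 1 |
| H | 2 | 2 | 1 |
| H and G | 2 | 2 | 2 |
| I | 0 | 1 | 1 |
| I and G | 1 | 2 | 2 |
| I and H | 2 | 2 | 1 |
| I, H and G | 2 | 2 | 2 |

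Rules A and B differ by exactly one point, and only for patients with ischaemic stroke and no intracranial haemorrhage. Rules B and C differ by one point, only for patients with intracranial haemorrhage and no gastrointestinal haemorrhage.

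**3. How far the two items overlap.** The bleeding item takes safety outcome events, which Outcome measures limits to major haemorrhages leading to admission and not post-traumatic. The stroke item carries neither limit. If the bleeding item inherits that definition, a traumatic or non-admitted intracranial haemorrhage scores 1, not 2. The overlap is therefore large but not complete.

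**4. What the other covariates can absorb.**

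- The difference between rules B and A is I × (1 − H). Among patients without both event types this equals I. If HAS-BLED has coefficient β, then β × score(B) = β × score(A) + β × I. A model that also holds an ischaemic-stroke indicator absorbs the shift exactly (coefficient 1 on I, residual 0).
- The difference between rules B and C is H × (1 − G). A single previous-bleeding indicator, max(H, G), equals 1 for both H alone and G alone, while the difference is 1 for the first and 0 for the second. One combined indicator cannot remove the extra point; separate indicators for the two sites could, except in patients with both.

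**The case against.** The strongest reply is that the article never says ischaemic stroke scores zero. The stroke sentence has no word such as *only*. It follows CHA2DS2-VASc text that expressly leaves haemorrhagic stroke out, so it may simply say where haemorrhagic events go. This stands in part: the zero is the natural reading, not an explicit one. But a programmer could code either rule, and the two differ by a point for a defined group of patients.

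A second reply is that the scale is declared as modified and its original item rules are not reproduced, so the article gives no standard against which double scoring of one haemorrhage is an error. This also stands. What can be said from the text is that the item's content does not match its label and that the double count is unexplained.

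A third concerns consequences. A reader might infer that the bleeding hazard ratios are confounded as a result. The article does not support that: previous ischaemic and bleeding events and CHA2DS2-VASc are listed as candidates in their own right, and matching on baseline characteristics may help further. That protection is not assured, because candidates must pass the 0.15 screen, *ischaemic events* may be broader than stroke, and a single bleeding indicator leaves the extra point in place.

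Three further inferences should be resisted: that every patient scoring the stroke item also scores the bleeding item (step 3 shows otherwise), that the 0 to 7 range is wrong (step 1 reproduces it), and that a particular share of the cohort is mis-scored. The article gives no prevalence, and the 12-month look-back limits how many past strokes are captured.

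**Conclusion.** The point holds as a defect in a scoring rule. Coded on its natural reading, the stroke item mostly repeats the bleeding item and omits the ischaemic strokes that its label covers. The size is one point for a patient with previous ischaemic stroke and no intracranial haemorrhage and, if double scoring is not intended, one point for a patient with a qualifying intracranial haemorrhage and no gastrointestinal haemorrhage. This mis-scores a baseline descriptor of bleeding risk and a named potential confounder. Bias in the adjusted hazard ratios is possible but not demonstrated, and the number of patients affected cannot be derived from the article.

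The conclusion rests on reading the stroke sentence as complete and on taking the item's label at face value. If the sentence only clarifies that haemorrhagic events count too, the ischaemic part falls away. The unexplained double count and the need to state the rule remain.

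**What to change.** In Outcome measures, under HAS-BLED:

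1. State that the cerebrovascular item is scored for any previous stroke, ischaemic or haemorrhagic, within the look-back period.
2. State whether one intracranial haemorrhage may score both the cerebrovascular and the bleeding item. If this is not intended, count each event in one item only: strokes and intracranial haemorrhage under the cerebrovascular item, gastrointestinal haemorrhage under the bleeding item. If it is intended, give the reason, as is done for labile INR and alcohol.

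The 0 to 7 range needs no change. The ischaemic stroke diagnoses are already extracted for CHA2DS2-VASc, so the cost is about one line in the derivation program and a sentence or two of text. No new data are needed.
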